#### End of study visit

Checkup (C3):
Clinical examinationsParaclinical examinationsBiological testsQuestionnaires: VAS (Fatigue, pain, and food intake), FACT-G, FACT-F, FACT-Cog, EQ-5D-3L, FAACT-AC/S, and HADSBlood samples for translational research (if consented)

Evaluation (E3):
Physical capacitiesQuestionnaires: VAS (fatigue and pain) and IPAQ

#### Follow-up visits

The investigator will follow patients for a maximum of 6 years after the end of the program.

Follow-up 1 (1st year):
Clinical examinations (every 3 months)Paraclinical examinationsQuestionnaires (every 3 months): VAS (fatigue and pain), FACT-G, FACT-F, FACT-Cog, EQ-5D-3L, FAACT-AC/S, and IPAQBlood samples for translational research (if consented)

Follow-up 2 (last 5 years):
Before disease progression (every 3 months)
❖ Biological tests❖ Clinical and vital signs❖ Survival status❖ Tumor evaluationAfter progression (every 3 months)
❖ Survival status until death or end of follow-up.

### Statistical plan

#### Sample size

The primary objective for the phase II is the feasibility of the study. The SPEP participation will be considered sufficient if a patient has performed at least 50% of the theoretically planned sessions within 3 months (supervised and non-supervised). With a unilateral alpha risk of 5%, a statistical power of 85%, a probability of inefficiency maximum of 50%, a probability of minimum efficiency of 65%, and a 5% lost to follow-up rate, 120 patients will need to be randomized in the phase II with a 2:1 ratio (74 patients in the SPEP; 37 patients in the control arm of recommended adapted physical activity). Patients will be included in a non-competitive manner in the different cohorts. An interim analysis is planned when 37 patients will be randomized in the SPEP arm with rejection of H0 if at least 27 patients have completed at least 50% of the planned sessions; rejection of H1 (futility) if 19 patients or less have completed at least 50% of the planned sessions.

The phase III study will evaluate the 3-month efficacy of the SPEP, compared to recommended adapted physical activity. The 120 patients randomized in the phase II will be included in the phase III analysis. The co-primary endpoint criteria are the fatigue score (using FACT-F) and the physical well-being score (using FACT-G) evaluated after 3 months. SPEP superiority over the recommended adapted physical activity program will be demonstrated if at least one of the criteria (FACT-F or FACT-G) increase significantly without deterioration of other criteria. To demonstrate a clinically significant difference of at least 5 points (standard deviation: 13) for the physical well-being dimension of the FACT-G questionnaire and at least 2.5 points (standard deviation: 6.5) for FACT-F questionnaire at 3 months [17, 18], with a bilateral alpha risk of 2.5%, a statistical power of 80%, and a 5% lost to follow-up rate, 312 patients will need to be randomized in the phase III. The inclusions will be non-competitive between the 4 cohorts (78 patients per cohort). A 30-month inclusion period is predicted for the recruitment of these 312 patients in 18 French centers. An interim analysis is planned at the end of the phase III corresponding to 39.5% of patients randomized in order to reject H0 or H1 according to alpha spending function.

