### Statistical analysis

For the phase II, all the analyses will be non-comparative and performed on the intention-to-treat (ITT) population: all patients included in the study irrespective of the respect of the study.

For the phase III, analyses will be performed on the modified ITT (mITT) population: ITT patients with FACT-F and physical well-being score available at baseline and M3. Longitudinal analysis of QoL data will be performed on a mITT2 population: ITT patients with FACT-F and physical well-being score available at baseline. Quantitative analyses will be described by the mean (standard deviation) and median (minimum-maximum) values while qualitative and categorical analyses will be reported by frequency and percentage. A description of FACT-F, FACT-G, and FACT-Cog scores will be done by arm for each time point with the mean (standard deviation) and median (minimum-maximum) values. The statistical analysis will be performed using t-test, log-rank, stratified log-rank, invariable analysis, and multivariable analysis.

For the co-primary endpoint, a t-test will be done to compare FACT-F and physical well-being scores at 3 months according to the study arms, at the statistical level of 2.5%, after checking the normality of the scores and potential transformation of the scores. An analysis of variance for repeated measure will also be done taking into account the baseline score. Then, some univariate and multivariate models will be done in order to identify factors associated with the change of fatigue and physical well-being score between baseline and 3 months. All factors with an univariate *p*-value < 0.1 will be eligible for the multivariate models.

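### Phase II: 74:37 is not a 2:1 split of 120, and with the printed interim limits 74 SPEP patients do not give both 5% alpha and 85% power; the 80 actually randomised give about 83%

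*Protocol article*

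**What the plan says.** All design figures are in the Sample size section of the protocol article.

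- **Error rates:** "With a unilateral alpha risk of 5%, a statistical power of 85" percent.
- **Rates compared:** "a probability of inefficiency maximum of 50" percent against "a probability of minimum efficiency of 65" percent. A patient is a success after performing at least half of the planned sessions in 3 months.
- **Numbers:** "a 5% lost to follow-up rate, 120 patients will need to be randomized in the phase II", with the arms given as "120 patients will need to be randomized in the phase II with a 2:1 ratio (74 patients in the SPEP; 37 patients in the control".
- **Interim look:** "rejection of H0 if at least 27 patients have completed at least 50% of the planned sessions; rejection of H1 (futility) if 19 patients" or fewer have done so. The look is tied to the randomisation of the 37th SPEP patient.
- **Analysis set** (Statistical analysis section): "For the phase II, all the analyses will be non-comparative and performed on the intention-to-treat (ITT) population", defined as everyone included.

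The article prints no final cut-off. A condensed article may leave that to the full protocol or the SAP, so its absence is not part of this point.

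**The concern.** The sentence presents 74 and 37 as the split of the 120 randomised, but they sum to 111. ITT removes nobody, so a decision rule built for 74 SPEP patients would be applied to about 80.

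The interim rule is written in counts. Its error rates can therefore be calculated exactly and compared with the claimed 5% and 85%. This is the test of the phase II primary endpoint. If the figures do not hold, either the risk of calling an inadequate programme feasible or the chance of recognising a feasible one differs from what is reported.

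Two smaller ambiguities affect the same test: whether the 65% already counts patients lost to follow-up as failures, and when the interim count is made.

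**Working it through.** **Inputs (Sample size section).** p0 = 0.50, p1 = 0.65, one-sided alpha 0.05, power 0.85, loss 5%, interim n = 37, efficacy at 27 or more, futility at 19 or fewer, 74 SPEP and 37 control, 120 in total.

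**1. Reproducing 74.** The normal approximation with the variance under the alternative only is

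n = (1.645 + 1.036)² × 0.65 × 0.35 / 0.15² = 72.7, so 73.

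This is within one patient of 74. The other usual single-stage calculations give more: 78 (77.1) with null and alternative variances, 80 (79.9) with the null variance, and 80 by exact binomial (cut-off 48, alpha 4.65%, power 85.4%).

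**2. Arm sizes.**
- 74 + 37 = 111.
- 111 / 0.95 = 116.8, so 117 (78 + 39).
- 120 at 2:1 = 80 + 40.
- Working back, 120 × 0.95 = 114 (76 + 38), which is not 74 + 37 either.

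**3. Exact error rates of the printed rule.** Let X1 ~ Bin(37, p) be the successes at the interim and X2 ~ Bin(n − 37, p) those after it. With final cut-off c,

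P(reject H0) = P(X1 ≥ 27) + Σ (x = 20 to 26) P(X1 = x) × P(X2 ≥ c − x).

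Alpha is this probability at p = 0.50, and power is its value at p = 0.65. At the interim, P(X1 ≥ 27) is 0.0038 at 50% and 0.201 at 65%. P(X1 ≤ 19) is 0.629 at 50% and 0.061 at 65%.

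| SPEP n | Final cut-off | Alpha | Power at 65% |
|---|---|---|---|
| 74 | 44 | 6.10% | 84.8% |
| 74 | 45 | 3.95% | 79.8% |
| 80 | 47 | 6.63% | 87.3% |
| 80 | 48 | 4.44% | 83.4% |
| 84 | 50 | 4.74% | 85.3% |

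A lower cut-off raises alpha and a higher one lowers power, so no cut-off at 74 meets both targets. Ignoring the interim does not rescue 74: cut-off 44 gives 6.5% and 86.8%, and 45 gives 4.0% and 81.1%. With the printed limits, 84 is the smallest SPEP number that meets both.

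**4. Losses.** Assume that 65% applies only to patients who are followed, and that the 5% lost count as failures under ITT. The success rate is then 0.65 × 0.95 = 0.6175. At n = 80 with cut-off 48 and the printed limits, power is 64.9%.

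**The case against.** The strongest reply is that 74 has a recognisable origin, that the loss allowance is in the same sentence, and that the trial will analyse about 80 SPEP patients rather than 74. Most of this stands.

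- **Origin of 74.** It follows from a standard approximation, so a reader should not infer that it is arbitrary. The approximation still does not make a count-based rule deliver 5% and 85%. Even on its own terms, if an O'Brien-Fleming-type look at 37 is assumed, power is 85.3% without a futility limit and 83.5% to 84.2% once the limit of 19 is added.
- **Nine missing patients.** A reader might infer that 9 patients are unaccounted for. The loss allowance explains 6 of them, and the last 3 may be rounding, for example to 30 in each of the 4 cohorts (an assumption). What remains is that 74:37 is labelled as the randomised split.
- **A 5-point loss of power.** That reading takes 79.8% at n = 74. The ITT set has about 80 SPEP patients, where power is 83.4%.
- **Futility limit above the null rate.** 19/37 is 51%, and a limit just above 50% is not an error. Its 6.1% chance of stopping when the true rate is 65% is a design choice, and the article sets nothing against it.
- **An interim bound to fail.** At the planned rate (312 / 30 × 2/3 = 6.9 SPEP patients a month), about 37 − 3 × 6.9 = 16 patients would have 3 months of follow-up when the 37th is randomised. It is tempting to conclude that the count could hardly exceed 19. But success needs 18 of 36 sessions, which at three a week can be reached at about week 6, and 37 − 1.5 × 6.9 is about 27 patients. The rule also counts completed participation, so it most naturally means the outcomes of the first 37. Only the wording of the trigger needs correcting.

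**Conclusion.** The point holds and should be fixed, but its practical size is modest. As written, 74:37 is not the split of 120 randomised, and 74 SPEP patients with the printed interim limits cannot have both 5% alpha and 85% power, whatever final cut-off the full plan uses. For the 80 SPEP patients implied by 120 at 2:1, a cut-off of 48 keeps alpha at 4.4% with power of 83.4%, which is 1.6 points below the stated figure.

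This rests on exact binomial calculation, on both interim limits being followed, and on all 80 being analysed. The more consequential uncertainty is the treatment of losses. If the 65% does not already include them as failures, power is about 65% under the assumption shown, and neither 85% nor 83% describes the test.

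**What to change.** 1. State 80:40 as the randomised split. If 74:37 means evaluable patients, label it so.
2. Set the final ITT success limit for 80 SPEP patients at 48 or more, before the outcome counts are seen.
3. With the printed interim limits, restate the exact error rates as alpha 4.4% and power about 83%.
4. Say whether the 65% already treats patients lost to follow-up as not successful. If it does not, report power of about 65% and the assumption behind it.
5. State that the interim count uses the outcomes of the first 37 SPEP patients once their 3-month programme period has ended, not at the randomisation of the 37th.

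Optionally, a futility limit of 17 or fewer with cut-off 48 of 80 gives alpha 4.7% and power 85.3% at a true rate of 65%. At 61.75% its power is about 67%, so it does not replace step 4.

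The cost is wording only, with no added patients. The interim result comes up to 3 months later than a literal reading of the trigger would give.

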### Statistical analysis

For the phase II, all the analyses will be non-comparative and performed on the intention-to-treat (ITT) population: all patients included in the study irrespective of the respect of the study.

For the phase III, analyses will be performed on the modified ITT (mITT) population: ITT patients with FACT-F and physical well-being score available at baseline and M3. Longitudinal analysis of QoL data will be performed on a mITT2 population: ITT patients with FACT-F and physical well-being score available at baseline. Quantitative analyses will be described by the mean (standard deviation) and median (minimum-maximum) values while qualitative and categorical analyses will be reported by frequency and percentage. A description of FACT-F, FACT-G, and FACT-Cog scores will be done by arm for each time point with the mean (standard deviation) and median (minimum-maximum) values. The statistical analysis will be performed using t-test, log-rank, stratified log-rank, invariable analysis, and multivariable analysis.

For the co-primary endpoint, a t-test will be done to compare FACT-F and physical well-being scores at 3 months according to the study arms, at the statistical level of 2.5%, after checking the normality of the scores and potential transformation of the scores. An analysis of variance for repeated measure will also be done taking into account the baseline score. Then, some univariate and multivariate models will be done in order to identify factors associated with the change of fatigue and physical well-being score between baseline and 3 months. All factors with an univariate *p*-value < 0.1 will be eligible for the multivariate models.

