#### Secondary outcomes

Progression free survival is defined as the time from randomization to date of disease progression or death of any cause, whichever occurs first.

Overall survival is defined as the time from the date of randomization to date death of any cause.

Toxicity of the targeted therapy will be assessed using the NCI-CTCAE v4.03. Data concerning the class, frequency, and severity of adverse events will be collected and analyzed. The data will be collected at baseline, monthly during the 3-month program, then every 3 months during the first year of follow-up.

Adherence to targeted therapy will be evaluated by the Morisky-Green questionnaire at baseline then monthly during the 3-month program. This questionnaire, composed of six items related to patient’s adherence to the scheduled treatment, is regularly used to evaluate adherence to oral therapies. Scoring is performed through sum of item scores. Higher scores indicate better adherence to treatment.

For the outcomes described below, patients will fill the French versions of the specific questionnaires at baseline, monthly during the 3-month program, then every 3 months during the first year of follow-up, otherwise indicated. For each questionnaire but EQ-5D-3L, scoring is performed through a simple sum of item scores using the scoring recommendations of the authors.

Quality of life (QoL) will be assessed using the FACT-G and the 3-level version of EuroQol-5D (EQ-5D-3L) questionnaires. FACT-G is composed of 27 items related to patient’s general well-being grouped into four well-being subscales: physical, social/family, emotional, and functional. One score is generated for each subscale and a global QoL score is generated from all items corresponding to the total FACT-G score. For each dimension, a higher score represents a better QoL level. EQ-5D-3L consists of a patient self-rate health on a visual analogue scale (VAS) plus a descriptive system of five dimensions: mobility, self-care, usual activities, pain/discomfort, and anxiety/depression. Each dimension has three levels of perceived problems. Patient decision results into a 1-digit number for each dimension that can be combined into a 5-digit number that describes the patient’s health state.

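### Read as written, the phase III population rule puts OS, PFS and toxicity in the month-3 completer set, excluding every patient who died before month 3

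*Protocol article*

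**What the plan says.** All of the population rules are in the protocol article, Statistical analysis.

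- Phase II: "For the phase II, all the analyses will be non-comparative and performed on the intention-to-treat (ITT) population".
- Phase III: "For the phase III, analyses will be performed on the modified ITT (mITT) population", defined as "ITT patients with FACT-F and physical well-being score available at baseline and M3".
- The one phase III exception: "Longitudinal analysis of QoL data will be performed on a mITT2 population", which needs the baseline scores only.
- Methods, in the same paragraph as the phase III rule: "The statistical analysis will be performed using t-test, log-rank, stratified log-rank, invariable analysis, and multivariable analysis".

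No other phase III set is named, and no safety set.

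The endpoints are defined under Secondary outcomes. For OS: "Overall survival is defined as the time from the date of randomization to date death of any cause". For PFS: "Progression free survival is defined as the time from randomization to date of disease progression or death of any cause". Toxicity is collected at baseline, monthly during the three-month program, and quarterly for the rest of the first year. Aim and research questions lists survival, toxicity, dose reduction and adherence as secondary objectives of both phases.

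**The concern.** A patient who dies before M3 cannot have an M3 score and so cannot be in the mITT set. For an endpoint whose clock starts at randomisation, this has three consequences:

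- **Guaranteed survival to M3.** No death before M3 can count, so the OS curve is flat at 100% over that period in both arms. Any effect on early deaths cannot be seen.
- **Selection after randomisation.** Membership depends on a measurement that prognosis influences. If completion differs by arm, the compared groups are no longer the randomised ones.
- **Lost toxicity data.** The monthly records of patients too ill to answer at M3 would be dropped, although they were collected.

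Unequal completion is plausible. The trial is open, and one arm has a coach at home every week while the other has a booklet. The Discussion says the secondary endpoints will be used to explore survival and a reduction in treatment toxicity, so these are comparisons the sponsor intends to interpret.

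**Working it through.** **Step 1. Do the survival tests fall under the mITT rule?** Phase II analyses are all non-comparative. A log-rank test between arms is comparative, so the log-rank and stratified log-rank tests belong to phase III. The only phase III sets named are mITT and, for longitudinal quality of life, mITT2. On the text, the tests fall under mITT.

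**Step 2. Who is excluded?**

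| Patient | In mITT? |
|---|---|
| Died before M3 | Never |
| Alive, no M3 scores | No |
| Stopped therapy or program, or progressed, but completed both scores at baseline and M3 | Yes |

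**Step 3. Reproduce the plan's own figure.** Inputs from Sample size: difference 5, SD 13 (or 2.5 and 6.5, the same standardised effect of 0.385), two-sided alpha 2.5%, power 80%, 5% loss. The 2:1 ratio is from Randomization.

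- Control: 1.5 × (13/5)² × (2.241 + 0.842)² = 1.5 × 6.76 × 9.505 = 96.4, rounded up to 97.
- SPEP: 2 × 97 = 194. Total: 291.
- With 5% loss: 291/0.95 = 306.3, rounded up to 307.

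This is within 2% of the stated 312. That number concerns the co-primary scores and does not change with the set used for survival. The plan's own 5% loss would be 0.05 × 312 ≈ 16 patients.

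**Step 4. Deaths before M3.** The documents give no rate. Assuming exponential survival, the share dying by 3 months is 1 − 0.5^(3/median):

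| Assumed median OS (months) | Share dead by M3 | Of 312 |
|---|---|---|
| 12 | 15.9% | 50 |
| 18 | 10.9% | 34 |
| 24 | 8.3% | 26 |
| 30 | 6.7% | 21 |

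Eligibility requires a life expectancy of at least 3 months, so the true share may be lower.

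**Step 5. Effect on the between-arm comparison.** This is an illustrative simulation, and every input is assumed: median OS 18 months, varying frailty between patients, follow-up cut at 36 months, and no true effect. M3 scores are missing for all who died before M3 and more often for sicker survivors. The result is the event-rate ratio, SPEP over control, in completers.

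| Excluded, control | Excluded, SPEP | Ratio in completers |
|---|---|---|
| 15% | 15% | 1.00 |
| 23% | 15% | 1.04 |
| 15% | 23% | 0.96 |
| 32% | 15% | 1.11 |

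In all patients the ratio was 1.00 in each row. Under these assumptions, equal loss gave no spurious difference. Unequal loss did, in favour of the arm that lost more of its sicker patients.

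**The case against.** The strongest reply concerns intent. The phase II sentence covers all analyses, while the phase III sentence says only analyses. The mITT set is defined by the two co-primary scores, and the paragraphs around it deal with those scores. The sponsor may have meant mITT for the M3 score comparison alone. The article is also a condensed text, and sets for secondary endpoints are often left to the full protocol or SAP. Follow-up of every patient from randomisation fits an ITT analysis of survival.

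Part of this stands: the documents do not prove that survival was meant to be analysed in mITT. But the article does not simply leave the set open. It states a general phase III set, makes one exception, and lists log-rank tests beneath it. A reader following it would use mITT.

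Four stronger readings are tempting, and the documents do not support them:

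- **Everyone who stopped or progressed early is removed.** Exclusion depends on missing scores, not on stopping. Under an assumed median PFS of 9 to 12 months, 16 to 21% (50 to 64 of 312) would have a PFS event by M3. That counts events, not patients lost, because those who progress and still answer at M3 remain with their events counted.
- **The cost-effectiveness analysis omits early deaths.** That analysis has its own methods under Ancillary outcome, and the Statistical analysis section does not mention it.
- **Toxicity rates will certainly be too low.** This is a risk; no figures are given that would establish it.
- **The mITT set should lose its role in the primary comparison.** That is a separate question and does not follow from this point.

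**Conclusion.** The point holds as a badly fixed analysis population for OS, PFS and toxicity, conditional on following the text literally. What is certain on that reading is that no death before M3 can count in OS or PFS. How many that would be rests on assumed exponential survival: about 21 to 50 of 312 for median OS of 12 to 30 months, and fewer if the eligibility criterion selects well. Bias between the arms requires unequal M3 completion. Its direction is unknown, and the simulated ratios of 0.96 to 1.11 are illustrations, not estimates for this trial.

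Severity is moderate. The endpoints are secondary, and neither the 312 patients nor the primary success rule is affected.

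**What to change.** Limit the mITT sentence to the M3 comparison of FACT-F and PWB, and leave mITT2 as it is. Then add two statements:

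- OS, PFS and the other secondary endpoints that do not depend on M3 scores, such as dose reduction and adherence, are analysed in all randomised patients (ITT).
- Toxicity is analysed in all patients who received oral targeted therapy, with no requirement for M3 questionnaires.

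The cost is two or three sentences, written before the analysis. No new data are needed: under Study visits, patients are followed from randomisation until death, withdrawal of consent or loss to follow-up, and Table 1 records survival status and toxicity at M1, M2 and M3. If the full protocol or SAP already limits mITT in this way, confirming that is enough.

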#### Interventional visits

During the intervention phase, the investigator and coach will perform the following checkups and evaluations:
➢ C1 and E1: 1 month ±3 days from SPEP initiation [experimental arm] or randomization [control arm]➢ C2 and E2: 2 months ±3 days from SPEP initiation [experimental arm] or randomization [control arm]

Monthly checkup and evaluation will be performed during the same day for each visit.

Monthly checkup (C1, C2): At the hospital, for all patients.
Clinical examinationsBiological testsQuestionnaires: VAS (fatigue and pain), FACT-G, FACT-F, FACT-Cog, EQ-5D-3L, FAACT-AC/S, and HADS

Weekly evaluations: At home, for patients in the experimental arm only.
Resting pulse rateQuestionnaires: VAS (fatigue and pain)

Monthly evaluations (E1, E2): At the hospital, for all patients.
Physical capacitiesQuestionnaires: VAS (fatigue and pain)

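### The phase III co-primary t-test is confined to patients with both scores at baseline and month 3, a completers' set that can bias the arm difference in either direction

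*Protocol article*

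**What the plan says.** All references are to the protocol article.

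- **Population (Statistical analysis).** Phase III analyses use the "modified ITT (mITT) population: ITT patients with FACT-F and physical well-being score available at baseline and M3". Phase II, by contrast, is analysed on all included patients.
- **Primary test (Statistical analysis).** The comparison named for the two co-primary scores is this: "a t-test will be done to compare FACT-F and physical well-being scores at 3 months according to the study arms, at the statistical level of" (the figure given is 2.5%).
- **Other planned analyses (Statistical analysis).** "Longitudinal analysis of QoL data will be performed on a mITT2 population: ITT patients with FACT-F and physical well-being score available at baseline". Straight after the t-test the article adds: "An analysis of variance for repeated measure will also be done taking into account the baseline score". It does not say which of the two populations this last analysis uses.
- **Data collected (Interventional visits and Table 1).** At the M1 and M2 checkups, all patients in both arms complete "VAS (fatigue and pain), FACT-G, FACT-F, FACT-Cog, EQ-5D-3L, FAACT-AC/S, and HADS". Table 1 schedules FACT-F and FACT-G at M1, M2 and M3 with no cut-off at progression.
- **Allowance for loss (Sample size).** The figure is given as follows, at 80% power and two-sided alpha 2.5%: "a 5% lost to follow-up rate, 312 patients will need to be randomized in the phase III".

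**The concern.** Answering both questionnaires at M3 is a post-randomisation event, so the set is not the randomised population, although its name contains ITT. Three features of this trial make that matter.

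1. **The reason for missing data is likely to be related to the outcome.** The Discussion calls the patients particularly frail and says fatigue may predict shorter survival. Entry requires a life expectancy of at least 3 months, which is the same length as the time to the primary assessment.
2. **Equal missingness cannot be presumed.** The trial is open-label. One arm has a weekly home visit from a coach and the other receives a booklet. This could act either way: more contact may help retention, while a demanding programme may cause withdrawals.
3. **The rule requires both scores.** A patient with a valid M3 FACT-F but no physical well-being score is dropped from the FACT-F test as well, and vice versa.

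At stake are the validity of the confirmatory comparison and, to a smaller degree, its power.

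**Working it through.** **Step 1. Reproduce the 312.** Inputs from Sample size and Randomization: difference 2.5 with SD 6.5 (FACT-F) or 5 with SD 13 (physical well-being), so d = 2.5/6.5 = 5/13 = 0.385 for both; two-sided alpha 2.5%; power 80%; allocation 2:1; 5% loss.

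n(control) = 1.5 × [(2.241 + 0.842)/0.385]² = 96.4, so 97 control + 194 SPEP = 291. Allowing for loss, 291/0.95 gives 307. With the t distribution, 98 + 196 = 294 are needed, and 294/0.95 gives 310. Rounding to four cohorts of 78 gives 312. The figure is sound on its own inputs.

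**Step 2. Power of a completers' t-test.** Non-central t, 2:1, d = 0.385, evaluable N = 312 × (1 − m). Only m = 5% comes from the document; the other rows are assumptions.

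| Missing at M3 (m) | Evaluable N | Power per endpoint |
|---|---|---|
| 5% | 296 | 81% |
| 10% | 281 | 78% |
| 15% | 265 | 76% |
| 20% | 250 | 73% |

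**Step 3. Selection bias with no true effect.** Assumption: a patient is missing when a latent health score, correlated r with the M3 score, falls below the cut-off that gives missing proportion p. The observed mean in that arm is then shifted upwards by

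SD × r × f(p), where f(p) = φ(z_p)/(1 − p),

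and the bias is the SPEP shift minus the control shift. Values: f(0.05) = 0.109, f(0.10) = 0.195, f(0.20) = 0.350.

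Worked example with 20% missing in SPEP, 10% in control and r = 0.5:
- Bias = 0.5 × (0.350 − 0.195) = 0.077 SD. This is 0.50 points on FACT-F (SD 6.5) or 1.0 point on physical well-being (SD 13), about one-fifth of either target difference (0.50/2.5 = 1.0/5).
- Observed n = 208 × 0.8 = 166 and 104 × 0.9 = 94. SE = 6.5 × √(1/166 + 1/94) = 0.84.
- Error favouring SPEP = P(Z > 2.241 − 0.50/0.84) = 5.0%, against a nominal 1.25%.

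| Missing, SPEP / control | r | FACT-F bias (points) | Error favouring SPEP |
|---|---|---|---|
| Equal in both arms | any | 0 | 1.25% |
| 10% / 5% | 0.5 | +0.28 | 2.9% |
| 20% / 10% | 0.3 | +0.30 | 3.0% |
| 20% / 10% | 0.5 | +0.50 | 5.0% |
| 20% / 10% | 0.7 | +0.71 | 8.0% |
| 10% / 20% | 0.3 | −0.30 | 0.5% |
| 10% / 20% | 0.5 | −0.50 | 0.2% |
| 10% / 20% | 0.7 | −0.71 | 0.1% |

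**Step 4. How much a mixed model would recover.** The 20%/10%, r = 0.5 scenario was simulated with baseline, M1 and M2 all observed and assumed between-visit correlations of 0.5 to 0.7. A missing-at-random analysis leaves about 0.03 to 0.05 SD of the 0.077 SD, so it removes roughly one-third to three-fifths of the bias. The rest stays because, in this scenario, missingness depends on the unseen M3 score itself.

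**The case against.** **A longitudinal analysis is already planned.** This is true and must be acknowledged: a baseline-adjusted repeated-measures analysis and the "mITT2 population: ITT patients with FACT-F and physical well-being score available at baseline" are both in the article. But the t-test is the test named for the co-primary endpoint at 2.5%, and the repeated-measures analysis is only an addition to it. The question is which analysis is primary, and that question stands.

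**Progressing patients are not dropped.** A reader might infer that patients who progress or become very ill are removed by rule. The document does not support this. Stopping at progression applies to the later follow-up period and to treatment observance, not to the M1 to M3 questionnaires. Illness excludes a patient only through a missing form; only death before M3 always excludes.

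**The bias is hypothetical.** This largely stands. The only loss figure in the document is 5%. With equal missingness and the same dependence on health in both arms, the bias is zero. If the booklet arm loses more patients, which weekly coaching makes at least as plausible, the error favouring SPEP falls below nominal. A reader might infer that the design leans towards a false claim for SPEP; the document gives no basis for a direction.

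**Power is a minor matter.** Also fair. The loss is 2 to 3 percentage points at 10% missing. Entry criteria (ECOG 2 or less, controlled pain) limit early attrition to some extent.

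**The statistical analysis plan may deal with it.** It could add imputation or sensitivity analyses, and their absence from an article is no fault. The primary population and test, however, are stated here, so the point does not rest on silence.

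**Conclusion.** The point holds in a limited form. The stated primary set for phase III consists of M3 completers on both questionnaires, so the confirmatory t-test does not compare all randomised patients, and a missing score on one endpoint removes the patient from the other.

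The possible bias, at assumed missingness of 20% against 10% in either direction and r from 0.3 to 0.7, is 0.3 to 0.7 FACT-F points in absolute value, against a target of 2.5. The error favouring SPEP is 3% to 8% if SPEP loses more patients, and 0.5% or less if control does, in which case a real benefit may be hidden. These are illustrations, not forecasts; the bias is zero if missingness is equal and equally related to health. The power loss is secondary, and the 312 itself is not in question.

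**What to change.** By documented protocol amendment, before any comparative analysis:

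- For each endpoint separately, make the primary analysis a mixed model for repeated measures on patients with a baseline score for that endpoint. Use the M1, M2 and M3 scores with arm-by-visit and baseline-by-visit terms, and test the M3 arm contrast at 2.5%.
- Keep the M3-completer t-test as supportive, without requiring the other questionnaire.
- Pair the model with a prespecified sensitivity analysis that treats death and dropout before M3 unfavourably.

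**Cost.** No new data, visits or patients; some extra programming. It is more than a wording change, because the article fixes the primary test and population, recruitment began in July 2017 and the trial is open-label. The amendment should therefore be dated and justified without reference to results by arm.

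**Downside.** The model assumes missing at random, so it only partly removes bias when missingness depends on the unseen M3 score (Step 4). It also implicitly assigns M3 scores to patients who died. A reader might take it as a full cure; it is not, which is why the sensitivity analysis belongs with it.
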